### Intervention

The two interventions, SOC and STRIPE, were developed with the Template for Intervention Description and Replication checklist for telehealth,^28^ Consensus on Exercise Reporting Template for exercise interventions^29^ and Toigo and Boutellier for resistance training interventions (online supplemental file 2–4).^30^

The intervention was modified from an existing protocol,^24^ and will consist of a 6-week intervention, totalling 18 rehabilitation sessions. Both groups will complete 3 weekly telemedicine sessions, each lasting 45–60 min. All participants will complete standardised exercises that include four components—hip extensor, hip abductor, core and quadriceps muscle groups. The SOC group will complete a strength training rehabilitation programme, whereas the STRIPE group will complete a strength training rehabilitation programme incorporating power-based exercises. Each week, SOC participants will complete three strength training sessions and STRIPE participants will complete two power and one strength training session. All participants will be provided a digital exercise pamphlet, including images with instructions, access to online videos of each exercise and general PFP educational information. Participants will be advised to avoid additional rehabilitation during the 6-week rehabilitation programme.

Strength and power-based rehabilitation sessions will adhere to guidelines from the American College of Sports Medicine (table 1).^31^ Starting load for both groups will be determined after the baseline session, to ensure each participant starts with the appropriate load. Participants will be provided varying levels of resistance bands at the initial visit to use throughout the intervention. Resistance will be monitored during the intervention to ensure exercises are challenging, but not resulting in volitional muscular failure. Hip abductor, hip extensor and core exercises will be initiated during week one and continued for the 6-week intervention, while quadriceps exercises will be introduced in the third week for both STRIPE and SOC groups.^24^

**Table 1 T1:** Descriptors of power-based and strength-based rehabilitation sessions

	Power-based exercises	Strength-based exercises
Load magnitude	60% 1RM	60%–70% 1RM
Sets and repetitions	4×6	3×12
Time under tension	<1 s concentric and 1 s eccentric	2 s concentric and 2 s eccentric
Rest between sets	3–5 min	2–3 min
Rest between repetitions	<1 s	<1 s
Rest between sessions	Minimum of 48 hours	Minimum of 24 hours

The intervention sessions will be administered through supervised telemedicine to expand access for participants. The telemedicine sessions will allow the research team to facilitate supervision, progress exercises, individualise the exercise components and assess adherence of all sessions. The research team will provide individualised care from a private laboratory space and participants will complete sessions at their location of choice. All sessions will be delivered individually, and each session will be scheduled between the research team and participant. Telemedicine sessions will be conducted on their university sponsored platform (WebEx, Zoom, Teams) and will use password protection and waiting rooms to protect participant privacy. We will not record or store any electronic protected health information during the sessions to protect HIPAA. The research team administering the intervention are licensed athletic trainers or credentialed physical therapists with multiple years of clinical experience treating musculoskeletal conditions, including PFP. All research team members administering the intervention will complete training by the PI prior to enrolment. Training will include exercise descriptors, exercise feedback in a telemedicine format, progression/regression instructions, recording adherences and monitoring adverse events. The PI will complete fidelity assessments on the training topics every 3 months. Research team members will provide verbal encouragement to participants, monitor adherence and record session data (sets, repetitions, exercises, resistance, pain and exertion).

Exercise progression or regression will be individualised to the participant’s daily pain level and perceived effort with the modified rate of perceived exertion (RPE) scale (0—very light activity to 10—maximal effort). The target goal is pain less than 3/10 on the VAS and participants reporting between 7 and 9 on the RPE scale. Participants who report pain greater than 3/10 on a specific exercise will regress by reducing load or the exercise. Participants who report pain less than 3/10 and less than 7 on the RPE scale will progress the exercise by increasing resistance or advancing the task. No additional criteria for discontinuation or modifying the intervention will be administered; however, participants may elect to withdraw from the study at any time and the reason for withdrawal will be requested.

### Demographics and outcome measures

Demographic variables (height, mass, age, sex, ethnicity, symptom duration, unilateral/bilateral symptoms) will be recorded at baseline. We will collect primary and secondary outcomes adhering to the study timeline (table 2). Participants will also complete a health history questionnaire, which includes questions related to previous treatment, pain location, aggravating factors, crepitus and pain quality. Baseline data, demographic variables and outcome measures will adhere to the REPORT-PFP checklist (Online supplemental file). We will instruct participants not to take pain medication for 48 hours prior to data collection of a primary outcome.^32^

**Table 2 T2:** Data collection timeline

		Baseline	Postintervention	6 months	12 months	18 months	24 months
Primary	Visual Analogue Scale	X	X	X	X	X	X
	Anterior Knee Pain Scale	X	X	X	X	X	X
	PFP recurrence			X	X	X	X
Secondary	Hip Rate of Torque Development	X	X				
	Fontal Plane Single Leg Squat Kinematics	X	X	X	X	X	X
Descriptive variables	PROMIS-10	X	X	X	X	X	X
	KOOS w/ PF-subscale	X	X	X	X	X	X
	Fear Avoidance Belief Questionnaire	X	X	X	X	X	X
	Pain Self-Efficacy Questionnaire	X	X	X	X	X	X
	International Physical Activity Questionnaire	X	X	X	X	X	X
	Global Rating of Change		X	X	X	X	X

KOOS, Knee injury and Osteoarthritis Outcome Score; PFP, patellofemoral pain; PROMIS-10, Patient-Reported Outcomes Measurement Information System-10.

### Primary outcomes

Pain will be measured with a VAS, quantifying the participant’s worst knee pain in the previous week. Pain will be assessed using a 10 cm line, with ‘no pain’ and ‘worst pain imaginable’ anchored on the left and right sides of the VAS, respectively. The distance between the left anchor and the participant denoted location will be measured as the worst pain score in the previous week. A change of 2 cm on a 10 cm VAS reflects the minimal clinically important difference in pain following treatment for patients with PFP.^33^ The VAS has fair to good test–retest reliability (Intraclass Correlation Coefficient (ICC)_(3,1)_ =0.56−0.83)) (1 week) and moderate concurrent validity (r=0.62 with AKPS and r=0.74 with Functional Index Questionnaire) in individuals with PFP.^33^ We will collect AKPS at baseline and all postintervention time points (table 2).

The AKPS is a 13-item questionnaire to assess self-reported knee function in patients with PFP. The AKPS ranges from 0 to 100 points, with lower scores representing greater knee disability. A 10-point change on the AKPS reflects the minimal clinically important difference in self-reported function following treatment for patients with PFP.^33^ The AKPS has good test-retest reliability (ICC _(3,1)_ =0.81) and moderate concurrent validity (r=0.70) with usual pain in the PFP population, and significant responsiveness.^33^ AKPS will be collected at baseline and all postintervention time points (table 2).

PFP recurrence will adhere to previously established methods^17^ and be assessed at four time points: 6, 12, 18 and 24 months following the intervention (table 2). Compensation will be provided to participants at each follow-up time point to improve retention. At each time point, participants will report if they experienced PFP in the previous 6 months and the average hours per week engaged in running or exercise in the previous 4 weeks.^17^ Recurrence will be defined as an event that requires treatment from a healthcare professional or being unable to participate in normal exercise for more than 2 days due to retropatellar or peripatellar pain.^17^ If additional clarification is required, follow-up will be completed with the research team member and participant through email.

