### Aims and objectives

The proposed study will compare a strength-based rehabilitation programme, the standard of care (SOC), to strength training rehabilitation incorporating power exercises (STRIPE). The exercises in both groups will target the hip abductors, hip extensors, core and quadriceps muscles. Our primary outcomes are self-reported knee pain measured by the Visual Analogue Scale (VAS), self-reported function measured by the Anterior Knee Pain Scale (AKPS) and recurrence rates. Recent evidence suggests that two in every three individuals with PFP report symptoms up to 2 years after seeking care^25^; therefore, we will assess PFP recurrence rates for 2 years. The proposed interventions target gluteal muscle function, which will be collected as secondary outcome variables (hip RTD and frontal plane kinematics).

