Frontal plane kinematics will be assessed during a single leg squat (SLS). Participants will wear tight-fitting clothes without shoes for the two-dimensional (2D) SLS assessment. Participants will complete an SLS on the pathological limb, with their contralateral limb flexed to 90° and arms placed across their chest.^35^ Participants will squat as low as possible and return to starting position.^35^ Coloured stickers will be placed on anatomical landmarks (sternum, bilateral anterior superior iliac spine (ASIS) and patella) to help quantify frontal knee, hip, pelvis and trunk kinematics. Video instructions will be provided to participants for sticker placement, camera placement and standardised squatting instructions. Squat speed will be standardised to a 2 s descend and 2 s ascend.^35^ Three practice trials will be provided before data collection, followed by 1 min rest, then three recorded trials. Researchers will assess and provide feedback on marker placement, camera placement and squatting performance at both baseline and immediate postintervention prior to data collection to improve accuracy. The feedback will serve as training for participants who will collect squatting performance remotely at the 6, 12, 18 and 24 months time points.

We will collect a global rating of change (GROC) score to quantify patient perceived change at all postintervention time points (immediate, 6- 12, 18 and 24 months). The GROC uses a single 7-point Likert-type scale with anchors of very much improved to very much worse. Also, each participant will be asked at the 6, 12, 18 and 24 months time points if they received additional care or treatment in the previous 6 months for their PFP. Those who have received care will be asked additional questions related to the type, reason and duration of care.

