Power analysis for the four postintervention (6, 12, 18 and 24 months) assessments was calculated with a Monte Carlo simulation involving 5000 replications of sample data using Mplus V.8.6 for the intercept-only structural equation model (SEM; growth curve model)^36^ assuming: (1) standardisation of all outcome variables at all time points, (2) *T*=five 6-month assessment time points (postintervention, 6, 12, 18 and 24 months follow-up), (3) all individual trajectories are horizontal but at different (intercept) levels, (4) randomisation results in equivalent groups, (5) intermittent missing outcome variable data will be MAR, increase every 6 months and monotonically from 1.1% at the first postfollow-up assessment to 9.1% at month 24 and (6) α=0.05 (two tailed). The dispositive power analysis question regarded statistical power levels to reject the treatment effect null hypothesis at various hypothetical sample sizes under the assumptions listed above. Power analysis results showed power would be >0.70 for any (intercept) effect size difference between STRIPE and SOC participants of d>0.55.

Power analysis for PFP recurrence was assessed with a binary logistic regression using the internal Monte Carlo simulation capabilities in Mplus V.8.6 assuming: (1) 50% of the STRIPE participants will have a PFP recurrence and 82% of SOC participants will have recurrence, (2) previous publications suggest PFP recurrence for SOC is 50%–90%,^6^ (3) MCAR missing data were included in the simulation and estimated to be 20% missing data in the outcome variable (PFP recurrence) and (4) α=0.05 (two tailed). Power analysis results showed power >0.80 if N=88 for analysis following missing data handling and the group (STRIPE vs SOC) term results in an OR>4.43.

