### Statistical analyses

We will use a MANCOVA to test for a significant treatment group (STRIPE vs SOC) main effect showing significantly greater improvement in each outcome variable at 6-week postintervention controlling for respective baseline values of each outcome variable. A multivariate intercept-only longitudinal SEM growth curve model will be used to determine if the difference in each outcome variable at 6-week postintervention is maintained at 6, 12, 18 and 24 months follow-up. The intercept-only SEM implies between-participant variability in the overall outcome variable, but the outcome does not change as a function of time. Finally, a binary logistic regression analysis will be used to determine if the intervention group (STRIPE vs SOC) significantly predicts PFP recurrence at the end of the 2-year follow-up. Dummy coded variables will be created and added to each analysis to account for cluster (site) differences and produce robust SEs. All missing data will be handled assuming MAR with maximum likelihood estimation consistent with currently accepted methodological research and practice.

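### The recurrence question looks back a fixed 6 months, so a participant who skips a follow-up and returns is never asked about the skipped interval (minor, cheap to fix)

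*Protocol article*

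**What the plan says.** Recurrence is one of three primary outcomes in the protocol article. Under Aims and objectives, "we will assess PFP recurrence rates for 2 years". Under Primary outcomes it will "be assessed at four time points: 6, 12, 18 and 24 months following the intervention", and at each of these "participants will report if they experienced PFP in the previous 6 months". The outcome is event-based: "Recurrence will be defined as an event that requires treatment from a healthcare professional", or more than 2 days unable to do normal exercise because of the knee pain. Under Secondary outcomes, participants are asked at the same four visits "if they received additional care or treatment in the previous 6 months for their PFP".

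Under Statistical analyses, one logistic regression tests whether group "significantly predicts PFP recurrence at the end of the 2-year follow-up".

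Sample size expects incomplete follow-up. For the growth-curve outcomes, "intermittent missing outcome variable data will be MAR, increase every 6 months and monotonically from 1.1" per cent, reaching 9.1% at month 24. For recurrence it assumes that 20% of outcomes are missing completely at random (MCAR).

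The only other contact described for recurrence is: "If additional clarification is required, follow-up will be completed with the research team member and participant through email".

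**The concern.** Four adjoining 6-month windows cover 24 months only if all four assessments are completed. Suppose a participant has a flare needing treatment at month 9, misses the 12-month assessment, and attends at 18 and 24 months. The two later questions cover months 12 to 18 and 18 to 24. Both can truthfully be answered *no*, and the month-9 event is never elicited. The care question leaves the same hole.

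The two answers are not symmetric. A reported recurrence settles the 2-year status whatever else is missing; an absence of reports with a gap does not. Unresolved status therefore arises only among participants with no observed event. Under the planned rates that is about twice as common in STRIPE as in standard of care (SOC).

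The loss occurs when the question is asked. An analysis plan can decide how to treat an unasked interval but cannot supply its content.

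**Working it through.** **Inputs from the protocol article.** Recurrence 82% SOC and 50% STRIPE, 20% missing, two-sided 0.05, N=88 (Sample size); equal groups, so 44 per arm (Randomisation). Intermittent missing rates 1.1% to 9.1% (Sample size, growth-curve simulation).

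**Assumptions.**
- The endpoint is cumulative over 2 years.
- Events are spread evenly and independently over four windows.
- Visits are missed independently.
- The growth-curve missing rates apply to recurrence visits, interpolated linearly. Scenario A puts 1.1% at the immediate postintervention visit, so months 6 to 24 have 3.1, 5.1, 7.1 and 9.1%. Scenario B puts 1.1% at month 6, giving 1.1, 3.8, 6.4 and 9.1%.

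**Plan's own figure.** Planned odds ratio (OR) = (0.82/0.18)/(0.50/0.50) = 4.56. With 20% missing there are 0.8 × 44 = 35.2 per arm. A two-proportion test with pooled variance then has power 0.823, or 0.811 at the stated OR of 4.43. A simulated Wald logistic test gives 0.820; a closed-form log-odds approximation gives 0.783. The stated power above 0.80 is broadly reproduced.

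**Event probability per window.** q = 1 − (1 − P)^(1/4).
- SOC: 1 − 0.18^(1/4) = 0.349
- STRIPE: 1 − 0.50^(1/4) = 0.159

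**One missed visit.** Status is unresolved if the other three windows are event-free, with probability (1 − q)³: 0.276 in SOC and 0.595 in STRIPE. The event lies only in the unasked window with probability q(1 − q)³: 0.096 in SOC and 0.095 in STRIPE.

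**All patterns.** With miss rate m_i at visit i:
- P(no event observed) = Π[1 − q(1 − m_i)]
- P(fully asked and no event) = Π(1 − m_i) × (1 − P)
- Unresolved = the first minus the second

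Scenario A has Π(1 − m_i) = 0.969 × 0.949 × 0.929 × 0.909 = 0.777.
- SOC: 0.205 − 0.777 × 0.18 = 0.065
- STRIPE: 0.524 − 0.777 × 0.50 = 0.135
- Together: 44 × (0.065 + 0.135) = 8.8 participants

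| | Scenario A | Scenario B |
|---|---|---|
| Gap before a later attended visit | 13.9% | 10.4% |
| Unresolved, SOC / STRIPE | 6.5% / 13.5% | 5.5% / 11.5% |
| Unresolved, of 88 | 8.8 | 7.5 |
| … of these attending month 24 | 5.2 | 3.9 |
| … of these with a hidden event | 1.2 | 0.9 |
| Gaps scored *no*, current question | 79.5% v 47.7%, OR 4.27 | 80.0% v 48.1%, OR 4.32 |
| Remaining gaps scored *no*, question reaching back to last assessment | 81.0% v 49.1%, OR 4.43 | 81.0% v 49.1%, OR 4.43 |
| Unresolved cases excluded, current question | 85.1% v 55.1%, OR 4.64 | 84.6% v 54.3%, OR 4.62 |

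The exclusion row divides observed recurrences by resolved participants. In Scenario A that is 0.795/(1 − 0.065) = 0.851 for SOC and 0.477/(1 − 0.135) = 0.551 for STRIPE.

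The comparator for the wording is OR 4.43, not 4.56. Participants whose last visits are missing stay unresolved under any wording (about 3.6 of 88). That this equals the OR quoted in Sample size is a coincidence.

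**Sensitivity to clustering.** If recurrences cluster within persons (beta-binomial, correlation 0.3 to 0.5, assumed), the gaps-as-*no* OR under the current question is 4.42 to 4.50. With the reworded question it is 4.50 to 4.53.

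**The case against.** **A condensed article.** Whether staff ask a returning participant about a skipped interval could sit in a visit manual, and the recurrence method follows a cited study that is not at hand. That is fair, and it lowers the weight of the point. But the article does not leave the look-back open: it states 6 months at each time point, and the care question repeats it. The email clause is for clarification and is not tied to a missed visit.

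**A last-window endpoint.** The Statistical analyses wording could mean recurrence in months 18 to 24 only, and missed intermediate visits would then not matter. Aims and objectives, and the summary box on what the study adds, speak of recurrence over 2 years, so the cumulative reading is better supported. It remains a reading.

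**Borrowed rates and independence.** The 1.1% to 9.1% belongs to the growth-curve outcomes. If missing visits were mostly dropout, few participants would return after a gap and the question's wording would matter less. Both objections stand, although the protocol does call the missingness intermittent.

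**Stronger readings the documents do not support.**
- *Recurrence will be miscounted.* No section scores an unasked interval as *no*. That branch is conditional.
- *The trial is underpowered because 4.27 is below 4.43.* The 20% allowance for missing recurrence exceeds the 8.5% to 10% unresolved here (7.5/88 and 8.8/88), and power of about 0.82 is reproduced with that allowance.
- *The treatment effect is seriously biased.* Outcome-dependent loss does not fit the MCAR assumption, but that assumption belongs to the power simulation. Excluding unresolved cases barely moves the OR.
- *One visit in five will be missed each time.* The protocol's 20% is the missing outcome overall, not a rate per visit.

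**Conclusion.** The point holds as a minor improvement to data collection. Followed as written, the two questions leave a skipped interval unasked, and status is then undeterminable for a returning participant with no recurrence reported elsewhere.

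Under the stated assumptions, rewording could settle about 4 to 5 of 88 participants who attend month 24, with about one hidden event among them. If gaps were scored *no*, the wording would account for an OR of 4.27 to 4.32 instead of 4.43. If unresolved cases were excluded, the OR would stay close to 4.56, but recurrence would be overstated by about 3 points in SOC and 4 to 5 in STRIPE. That matters for a trial that intends to report recurrence rates.

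The effect is smaller if recurrences cluster within persons or missed visits are mostly dropout. It disappears if the endpoint is the last window only.

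**What to change.** Keep the 6-month item for participants on schedule. For anyone who has missed an assessment, ask both the recurrence and the care question about the time *since your last completed study assessment*, with that date filled in, or since the end of the programme if none was completed. Record the approximate month of each event.

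Derive 2-year status as *yes* if any qualifying event is reported, *no* only if the reported intervals together cover all 24 months, and otherwise incomplete at the last covered date.

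The cost is one wording change in the follow-up questionnaire and one derivation rule, with no extra visits. The downside is recall over 12 months or more for the few who skip a visit. That error is not modelled here and could matter for events as small as a few days off exercise. Participants who never return remain unresolved. The change must be made while follow-up is still being collected.

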## Introduction

Patellofemoral pain (PFP) is one of the most common knee pathologies in the general population and military personnel.^1^ The incidence of PFP in the military ranges from 9.7 to 571.4 per 1000 person-years, with females at 2.2 times greater risk than males.^1 2^ The annual prevalence rate in the general adult population is 22.7%.^1^ PFP accounts for 7% of all diagnoses in patients who seek medical care^3^ and up to 25% of all treatment for knee-related injuries within sports medicine clinics.^4^ Persistent knee pain, disability and impaired joint-related and health-related quality of life are common in individuals with PFP.^5 6^

The aetiology of PFP is unknown. Increased stress on the patellofemoral joint due to altered lower extremity mechanics is proposed to be the primary mechanism of PFP.^7^ Altered movement patterns are common in individuals with PFP during tasks, such as single-leg squat, stair ambulation and running,^8 9^ and are associated with greater knee pain and worse subjective function.^10^ Hip musculature is a major influence on the control of these lower extremity mechanics, and adults with PFP are 20%–28% weaker in hip strength when compared with asymptomatic adults.^11 12^

Clinicians prescribe strengthening exercises focused on weak gluteal muscles,^13 14^ which produces positive short-term outcomes but suboptimal long-term outcomes. Over 90% of patients with PFP report knee pain and symptoms greater than 15 years following initial diagnosis.^6^ While most patients with PFP seek medical care,^8^ over 60% are not satisfied with their knee function within 3 months of concluding treatment.^15^ Numerous studies targeting hip abductor strength produce minimal improvements,^16^ and hip strength gains are lost within months of concluding treatment.^16 17^

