### Study hypothesis

The study hypothesis is that participants assigned to the STRIPE group will have a greater decrease in pain, greater improvements in self-reported function and lower PFP recurrence rates compared with those in the SOC group. Additionally, participants in the STRIPE group will have greater improvement in hip RTD and frontal plane kinematics compared with SOC.

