### Eligibility and screening

Participants will be sought through flyers, social media posts, sports medicine physician referrals, and participation in previous PFP studies. Participants will be 18–40 years old and screened for eligibility with the inclusion/exclusion criteria defined by the Patellofemoral Pain Consensus statement^27^ (box 1). The intervention will be delivered through telemedicine, requiring participants to have a computer with internet access and camera/audio capabilities. Each site’s principal investigator (site-PI) will screen participants to ensure eligibility and consent participants. The three investigators at each site will complete an eligibility training and screening procedures session before participant enrolment.

Box 1Inclusion and exclusion criteriaInclusion criteriaInsidious onset of peripatellar or retropatellar pain greater than 3 months.Worst pain in the previous month of 3/10 with two of the following tasks:Prolonged sitting.Jumping.Squatting.Kneeling.Running.Stair ambulation.Exclusion criteriaOther forms of anterior knee painOsgood-Schlatter.Tendon pain.Bursitis.History of lower extremity surgery.History of patella subluxation.Meniscal injury, assessed by clustered special tests: history of ‘catching’ or ‘clocking’, pain with forced hyperextension, pain with maximal knee flexion, pain with McMurray test and joint line tenderness.Ligamentous instability, assessed by the anterior drawer, Lachman, posterior drawer, varus/valgus stress tests.Referred pain from the lumbar spine.Mental capacity for human subjects to consent to participating in the study.

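### As defined, recurrence requires no prior recovery, so this primary outcome mixes persistent pain with relapse and a group difference would not by itself show lower recurrence

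*Protocol article*

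**What the plan says.** Recurrence is one of three primary outcomes (Aims and objectives), and the study hypothesis is that STRIPE will give "lower PFP recurrence rates compared with those in the SOC group".

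Under Primary outcomes, the rule is "Recurrence will be defined as an event that requires treatment from a healthcare professional or being unable to participate in normal exercise for more than" a set limit (2 days), where the cause is retropatellar or peripatellar pain. It is assessed at 6, 12, 18 and 24 months. At each of these visits "participants will report if they experienced PFP in the previous 6 months". The section adds that "PFP recurrence will adhere to previously established methods", citing reference 17.

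Eligibility and screening requires "onset of peripatellar or retropatellar pain greater than 3 months", so every participant has long-standing pain at entry.

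Sample size powers the comparison on 50% (STRIPE) v 82% (SOC) with N=88. Statistical analyses specifies a binary logistic regression on group at the end of the 2-year follow-up. Neither section restricts the analysis to participants who recovered or says how those who did not recover are handled.

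**The concern.** Relapse can only happen to someone who has first got better. The printed rule sets no recovery threshold, no symptom-free interval and no required response at the postintervention visit. Take a participant whose pain did not change over the 6 weeks. The advice in the Intervention section to avoid other rehabilitation applies only during the programme, so this person may seek care from week 7 and is then a recurrence at 6 months.

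By the article's own account this is not a rare case. The Introduction says that "over 60% are not satisfied with their knee function within 3 months of concluding treatment".

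The article also uses persistence figures to support recurrence. Aims and objectives justifies the 2-year recurrence follow-up by the statement that "two in every three individuals with PFP report symptoms up to 2 years after seeking care". Sample size says "previous publications suggest PFP recurrence for SOC is 50%–90" per cent and cites reference 6, which the Introduction cites for knee pain and symptoms more than 15 years after diagnosis.

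At stake is what the trial may conclude. If STRIPE makes more people better at 6 weeks and has no effect on relapse, the plan could still report that power exercises lower recurrence. The opposite error is also possible: persistent cases in both arms can dilute a real fall in relapse.

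**Working it through.** **1. The plan's own figure.** Inputs from Sample size: 50% v 82%, two-sided α 0.05, N=88 (44 per arm), 20% missing (35.2 per arm). Formula: power = Φ{[|p₁−p₂|√n − 1.96√(2p̄(1−p̄))] / √[p₁(1−p₁)+p₂(1−p₂)]}.
- n=44: (0.32×6.633 − 1.96×0.670)/0.631 = 1.28, power 0.90.
- n=35.2: (0.32×5.933 − 1.96×0.670)/0.631 = 0.93, power 0.82.

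The stated power above 0.80 reproduces. The odds ratio for 50% v 82% is (0.82/0.18)/(0.50/0.50) = 4.56, close to the printed 4.43. The power figure is not in dispute; the question is what the event measures.

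**2. What the event rate is made of.** Let u be the share not recovered at postintervention, c the share of those who meet the event rule, and r the relapse risk among the recovered. Then

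event rate = u·c + (1−u)·r.

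The article gives none of u, c or r, so all values below are assumptions. Relapse risk is the same in both arms on every row, so any contrast comes from non-recovery alone. P(sig) is the chance of a significant result from the formula in step 1, at 44 and at about 35 per arm.

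| Assumed u, SOC v STRIPE | c | r, both arms | Event rate, SOC v STRIPE | P(sig), 44 / 35 per arm |
|---|---|---|---|---|
| 0.60 v 0.40 | 0.9 | 0.50 | 74% v 66% | 0.13 / 0.11 |
| 0.40 v 0.20 | 1 | 0.40 | 64% v 52% | 0.20 / 0.17 |
| 0.60 v 0.20 | 1 | 0.40 | 76% v 52% | 0.65 / 0.55 |
| 0.70 v 0.20 | 1 | 0.40 | 82% v 52% | 0.86 / 0.77 |
| 0.74 v 0.29 | 1 | 0.30 | 82% v 50% | 0.89 / 0.81 |

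First row: 0.60×0.9 + 0.40×0.5 = 0.74 and 0.40×0.9 + 0.60×0.5 = 0.66. Last row: 0.74 + 0.26×0.30 = 0.818 and 0.29 + 0.71×0.30 = 0.503.

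**3. How plausible the rows are.** On a latent normal scale (an assumption), recovery of 26% v 71% in the last row is a difference of 0.643 + 0.553 = 1.20 SD. That is more than twice the d of 0.55 that the trial is sized to detect for the postintervention outcomes. Recovery of 40% v 60% in the first row is 0.253 + 0.253 = 0.51 SD, close to the planned size.

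**4. Dilution in the other direction.** If u and c are equal in both arms, the u·c terms cancel and the difference in event rates is (1−u)×(r_SOC − r_STRIPE). At u=0.60, a true difference in relapse shows at 40% of its size.

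**5. Restricting to recovered participants.** Recovery is observed after randomisation, so this subset is no longer a randomised comparison. It also costs power. With 50% v 82% and recovery of 80%, 60% or 40% in both arms, power is 0.82, 0.70 or 0.52 with complete data, against 0.90 in all 88. With 20% missing it is 0.73, 0.60 or 0.43, against 0.82.

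**6. Requiring a lower share of 'recovered then event' for a claim of lower recurrence.** In the last row of the table, suppose STRIPE truly halves relapse from 30% to 15%. The share of those randomised who recover and then have an event is 0.71×0.15 = 10.7% for STRIPE and 0.26×0.30 = 7.8% for SOC. Such a rule would deny a real halving, because better recovery enlarges the group at risk.

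**The case against.** Five points can be made for the plan.

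- **The rule counts an event, not pain.** A reader might infer that everyone who never recovers is scored as a recurrence. The text does not say so: persistent pain with no professional care and no more than 2 days of lost exercise is not counted. This stands, and it makes the rows with c=1 upper limits for their recovery and relapse inputs.
- **The comparison is valid.** A reader might infer that the trial can say nothing useful about this outcome. That goes too far. All randomised participants are compared on an event that matters to patients. What stands is narrower: the analysis does not identify which component drives a difference.
- **Recurrence might be thought merely to repeat VAS and AKPS.** The documents do not show this. VAS covers worst pain in the previous week, whereas recurrence covers 6-month windows and concerns care or lost exercise. No overlap figure is given.
- **The cited method may contain a recovery condition.** Reference 17 is not at hand, so this is open. But the article prints an explicit rule, and that rule has no such condition.
- **Further data are collected.** Secondary outcomes includes questions on the type, reason and duration of additional care, and Primary outcomes allows clarification by email. These could help to identify continuing care, but the article does not link them to the recurrence definition.

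**Conclusion.** The point holds in a limited form. As printed, the endpoint is persistent or recurrent patellofemoral pain that leads to care or to lost exercise. The randomised comparison of that event stands, and so does the power calculation. The hypothesis of lower recurrence does not follow from a significant result alone, because better initial response with unchanged relapse would move the endpoint in the same direction.

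The size is uncertain. With equal relapse in both arms, the assumed inputs give anything from 74% v 66%, which would rarely reach significance (0.13 at 44 per arm), to about the planned 82% v 50%. The upper end should not be read as a forecast: its recovery rates were chosen to match the planning contrast and imply a response difference far above the one the trial is sized for. The conclusion rests on the printed rule being complete. If reference 17 adds a recovery condition that will be applied, what remains is to print it and to say how unrecovered participants are handled.

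**What to change.** 1. Keep all randomised participants in the primary comparison.
2. If the cited method contains a recovery condition, print and apply it, and say how participants who never recovered are handled. Otherwise name the endpoint for what it measures, for example *persistent or recurrent PFP event by 24 months*, and word the hypothesis to match.
3. Before unblinding, fix a recovery criterion based on the postintervention VAS and/or GROC, both already collected. In choosing it, consider the article's own 2 cm minimal important difference and test–retest ICC of 0.56–0.83 for the VAS, so that a trivial shift across a cut-off is not called recovery.
4. Report by arm, as proportions of those randomised, the full cross-classification: not recovered with an event, not recovered without an event, recovered then event, and recovered without an event. Show unknown status separately.
5. Treat this breakdown as descriptive and limit the confirmatory conclusion to the composite event. Do not make a claim depend on a lower share of 'recovered then event' (step 6 of the working), and do not replace the primary comparison with one among recovered participants (step 5).

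The cost is a change of wording and one derived variable. No extra visits or participants are needed. The downside is a narrower headline claim.
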